**Study Procedures**

| **Visit** | **Screening[1]** | | **Treatment period** | | | | **Post-treatment** | | | **Follow-up of survival** | | |
| --- | --- | --- | --- | --- | --- | --- | --- | --- | --- | --- | --- | --- |
|  |  |  |  |  |  |  | **Withdrawal** | **End-of-**  **treatment** | **Before progression[2]** | | **After progression** | **After DCO[3]** |
|  | 1 | 2 | 3 | 4 | 5+ | 6+[4] | NA | NA | NA | | NA | NA |
| **Visit windows** | -28-0 | -7-0 | ±3 | ±3 | ±3 | ±3 | ±3 | ±3 | ±7 | | ±7 | ±7 |
| **Treatment cycles** | NA | NA | C1D7 | C1D21 | C3D21 | C5D21+ | NA | NA | NA | | NA | NA |
| **Study weeks** | -4-0 | -1-0 | 1 | 3 | 9 | 15+ | NA | With 21 days after treatment discontinuation | Every 6 weeks | | Every 6 weeks | Every 8 weeks |
| **Baseline characteristics** | | | | | | | | | | | | |
| **Informed consent** | X |  |  |  |  |  |  |  |  | |  |  |
| **Demographics** | X |  |  |  |  |  |  |  |  | |  |  |
| **Inclusion/exclusion criteria** | X |  |  |  |  |  |  |  |  | |  |  |
| **Enrollment ID** |  | X |  |  |  |  |  |  |  | |  |  |
| **Physical examination [5]** |  | X | X | X | X | X | X |  |  | |  |  |
| **Vital signs [6]** |  | X | X | X | X | X | X |  |  | |  |  |
| **Medical history [7]** | X |  |  |  |  |  |  |  |  | |  |  |
| **Compliance before enrollment [8]** |  | X |  |  |  |  |  |  |  | |  |  |
| **Radiographic evidence of progression** | X |  |  |  |  |  |  |  |  | |  |  |
| **Laboratory evaluations** | | | | | | | | | | | | |
| **Hemanalysis [9]** |  | X | X | X | X | X | X | X |  | |  |  |
| **Urinalysis [10]** |  | X | X | X | X | X | X | X |  | |  |  |
| **Stool tests [11]** |  | X | X | X | X | X | X |  |  | |  |  |
| **Blood biochemistry [12]** |  | X | X | X | X | X | X | X |  | |  |  |
| **Coagulation function [13]** |  | X | X | X | X | X | X |  |  | |  |  |
| **Thyroid function [14]** |  | X | X | X | X | X | X |  |  | |  |  |
| **Tumor marker** |  | X | X | X | X | X | X |  |  | |  |  |
| **12-ECG [15]** |  | X | X | X | X | X | X |  |  | |  |  |
| **Myo-cardial enzymonram [16]** |  | X |  |  |  |  |  |  |  | |  |  |
| **Echocardiography [17]** |  | X |  |  |  |  | X |  |  | |  |  |
| **Hepatitis B, Hepatitis C, HIV [18]** | X |  | | | | | | | | | | |
| **Pregnancy test [19]** |  | X |  |  |  |  | X |  |  | |  |  |
| **Imaging assessment** | | | | | | | | | | | | |
| **Imaging assessment [20]** |  | X |  | X | At the end of every two cycles (6 weeks ±7 days) | | X |  | X | |  |  |

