| **Examination of brain lesions [21]** |  | X |  | X | At the end of cycle 3 (±7 days) and every 4 weeks thereafter (12 weeks ±7 days) | | X |  | X | |  |  |
| **Other clinical assessments** | | | | | | | | | | | | |
| **ECOGPS** |  | X |  | X | X | X | X | X |  | |  |  |
| **Neurological function evaluation and corticosteroid use** |  | X |  | X | At the end of cycle 3 (±7 days) and every 4 weeks thereafter (12 weeks ±7 days) | | X |  | X | |  |  |
| **Blood pressure monitoring [22]** | X | X | X | X | X | X | X |  |  | |  |  |
| **Adverse events [23]** |  |  | X | X | X | X | X | X |  | |  |  |
| **PD-L1 expression [24]** | X |  |  |  |  |  |  |  |  | |  |  |
| Study drugs | | | | | | | | | | | | |
| **TQB2450** |  | | 3-week cycle, given on day 1 in a cycle | | | |  |  |  | |  |  |
| **Anlotinib** |  |  | 3-week cycle (2 weeks on and 1 week off) | | | |  |  |  | |  |  |
| **Distribution/recycling of anlotinib** |  | X |  | X | X | X | X |  |  | |  |  |
| **Concomitant treatments [25]** | X | X | X | X | X | X | X | X | X | | X | X |
| **Drug compliance [26]** |  |  | X | X | X | X | X |  |  | |  |  |
| **Follow-up of survival [27]** | | | | | | | | | | | | |
| **Time to disease progression [28]** |  |  |  |  |  |  | every 6 weeks (±3 days) until disease progression or initiating other anti-tumor therapy (non-imaging PD patients) | | | |  |  |
| **Time to death** |  |  |  |  |  |  |  |  |  | | X | X |
| **Tomur treatment [29]** |  |  |  |  |  |  |  | X | X | | X | X |

Note: All observation indicators and examination schedule will not be affected by duration of treatment discontinuation, but occasional changes in each wisit window due to holidays or other administrative reasons are allowed.

The window period of 3 days for screening indicators and examination must be completed before the initiation of the treatment cycle, for example, screening should not be repeated if performed within 7 days before the initiation of the first cycle of treatment. NA: not applicable.

1. Subjects must complete the screening visit within 28 days after imaging progression;
2. Subjects who withdraw from the study without objective progress will continue to be followed up until the date of objective progress occurred or data cut-off;
3. DCO: Data cut-off;
4. Subjects are visited every 6 weeks from V5;

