5. Physical examination: Whole body system examination (facial features, integumentary system, lymph nodes, eyes, ears, nose, throat, abdomen, spine, extremities, and nervous system) are performed within 7 days before enrollment, at C1D7, C1D21, and thereafter at days 21 of every two cycles (odd numbered cycles), and at dropout visit;
6. Vital signs: Temperature, pulse rate, and respiratory rate are performed within 7 days before enrollment, at C1D7, C1D21, and thereafter at days 21 of every two cycles (odd numbered cycles), and at dropout visit; Blood pressure monitoring is described in [22];
7. Medical history: Pathological results, EGFR T790M mutation test report; history of tumor surgery, chemotherapy, radiotherapy, and other disease treatment;
8. Compliance before enrollment: Days between the first progression of the subject and enrollment;
9. Hemanalysis: Hemoglobin, red blood cells, white blood cells, neutrophil count, lymphocyte count, and platelets count are performed within 7 days before enrollment, at C1D7, C1D21, and thereafter at days 21 of every two cycles (odd numbered cycles), and at dropout visit, and at days 21 after treatment. If the neutrophil count ≤1×109/L or platelets (PLT) ≤50×109/L, additional examination (1 time/2-3 days) is required; weekly hemanalysis is required if there is a delay in dosing or dose adjustment due to hematological toxicity;
10. Urinalysis: Urine protein, glucose, occult blood (red blood cell and white blood cell), pH, and ketone bodies are performed within 7 days before enrollment, at C1D7, C1D21, and thereafter at days 21 of every two cycles (odd numbered cycles), and at dropout visit, and at days 21 after treatment; If the semi-quantitative method shows the levels of protein ≥2+ (e.g., urine test strip), 24-hour urine protein quantification should be performed;
11. Stool tests: Occult blood test is performed within 7 days before enrollment, at C1D7, C1D21, and thereafter at days 21 of every two cycles (odd numbered cycles), and at dropout visit.

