12. Blood biochemistry: Liver function (TP, A, G, ALT, AST, LDH, ALP, TBil, DBil, and IBil), renal function (BUN, Cr, and UA), blood lipid tetrachoric (TC, TG, HDL, and LDL), electrolytes (K+, Na+, CL-, Ca2+, Mg2+, and P), lipase, amylase, fasting glucose, etc. are performed within 7 days before enrollment, at C1D7, C1D21, and thereafter at days 21 of every two cycles (odd numbered cycles), and at dropout visit, and at days 21 after treatment; During the drug administration, patients who develop early symptoms of liver injury (e.g., appetite loss, vomiting, right upper abdominal discomfort, malaise, etc.) before blood biochemical abnormalities should undergo blood biochemistry immediately. If ALT or AST is up to 3 times ULN or baseline value and total bilirubin up to 2 times the ULN or baseline value, the frequency of tests should be increased (recommended 1-2 times/week);
13. Coagulation function (PT, APTT, TT, Fbg, and INR) are performed within 7 days before enrollment, at C1D7, C1D21, and thereafter at days 21 of every two cycles (odd numbered cycles), and at dropout visit.
14. Thyroid function (T3, T4, FT3, FT4, and TSH) are performed within 7 days before enrollment, at C1D7, C1D21, and thereafter at days 21 of every two cycles (odd numbered cycles), and at dropout visit.
15. 12-ECG are performed within 7 days before enrollment, at C1D7, C1D21, and thereafter at days 21 of every two cycles (odd numbered cycles), and at dropout visit. If an abnormal ECG is identified, two additional confirmations must be performed (each 5 minutes apart and the QTc interval should be indicated);
16. Myo-cardial enzymonram is detected within 7 days before enrollment. This examination is supplemented only when symptoms such as precordial pain, palpitations, and ECG abnormalities are present;
17. Echocardiography is performed within 7 days before enrollment and at dropout visit. This examination is supplemented only when clinically meaningful ECG abnormalities occur during treatment;
18. Hepatitis B virus (HBV) and hepatitis C virus examination: HBV examination (HBsAg, HBsAb, HBeAg, HBeAb, and HBcAb) is performed and if the test result is abnormal, viral replication (HBA DNA) and hepatitis C virus antibody (anti-HCV) test should be conducted;
19. Pregnancy testing is limited to women of childbearing age, who are required to undergo a pregnancy test within 7 days before enrollment;

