Subjects who discontinue the study should continue to be monitored for AEs. If feasible, these subjects should be followed up for AEs until resolution to baseline levels or when the investigator determines it unnecessary to continue monitoring. In cases of chronic conditions such as AEs, the investigator might agree to discontinue further follow-up. In such instances, the investigator must document their decision in the subject's original medical records and promptly inform the sponsor about the participant's study discontinuation

During the study, participants who received medication but did not complete the required study assessments should have their final evaluation based on their last available data. Investigators are to contact participants who missed follow-up visits and document the evidence of contact in relevant source documents and Electronic Data Capture (EDC) systems (e.g., timestamps and dates of phone calls, mailing receipts), ensuring proper record-keeping.

For the following reasons leading to withdrawal, subsequent data collection requirements are waived:

1. Withdrawal of informed consent by the participant
2. Inability to complete follow-ups as scheduled for various reasons
3. Death
4. Sponsor's termination of the study

All patients must read and sign an informed consent approved by the ethics committee before the initiation of the study. All study procedures are required to be performed according to the time window in the schematic flow diagram, which is independent of the duration of drug discontinuance. However, the study procedures are allowed for modification within the time window due to holidays or other reasons.

1. **Study drugs**
   1. **Basic information about the study drugs**

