- Toxic reactions should be graded according to the NCI CTCAE 5.0;
- In case of simultaneous occurrence of severe toxicity of different severity levels, adjustments should be made according to the highest level observed;
- Treatment delays due to toxicity caused by anlotinib capsules could be delayed up to 35 days after the start of day 1 of the cycle (i.e., a 14-day delay in planned treatment) to allow adequate time for the subject to recover from any toxic effects caused by anlotinib hydrochloride. If a subject is unable to resume treatment by day 35 after the last dose, the subject must discontinue anlotinib hydrochloride treatment;
- Treatment delays due to toxic reactions caused by TQB2450 could be delayed up to 12 days after the start of day 1 of the treatment cycle;
- If subjects require permanent discontinuation due to toxic reactions (e.g., immune-related pneumonitis) of TQB2450, monotherapy with anlotinib should be continued until disease progression or unacceptable toxicity (whichever occurs first);
- If subjects require permanent discontinuation due to toxic reactions (hypertension, proteinuria, etc.) of anlotinib, monotherapy with TQB2450 should be continued until disease progression or unacceptable toxicity (whichever occurs first);
  - - 1. **Criteria for Dose Delay**

All of the following conditions should be met before starting treatment in any cycle, otherwise, a delay in administration is required:

- Absolute neutrophil count ≥1.5×109/L;
- Platelet count ≥75×10^9^/L;
- Hemoglobin（Hb）≥80g/L;
- Proteinuria ≤2+;
- Hand-foot skin reaction and hypertension ≤grade 2;
- Other toxicities until recovery to ≤grade 1

During the administration period (1-14 days) of anlotinib every cycle, if toxic reactions occur and the medication needs to be delayed, the maximum delay time should not exceed 5 days. If the medication cannot be continued for more than 5 days, the remaining anlotinib will not be administrated in this cycle.

- - - 1. **Dose modification**

Dose modifications for the TQB2450 were not allowed in principle throughout the study.

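### Every cycle start depends on laboratory limits, but no blood count, urinalysis or biochemistry is scheduled just before cycles 3, 5, 7 and later odd cycles

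*Protocol*

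**What the plan says.** Section 5.5.3.2 (Criteria for Dose Delay) states: "All of the following conditions should be met before starting treatment in any cycle, otherwise, a delay in administration is required". The list covers neutrophils of at least 1.5×10^9/L, platelets of at least 75×10^9/L, hemoglobin of at least 80 g/L, proteinuria no higher than 2+, hand-foot reaction and hypertension no higher than grade 2, and all other toxicities at grade 1 or lower. Section 5.5.1 gives TQB2450 on day 1 of every 21-day cycle and anlotinib for two weeks on, one week off.

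The Study Procedures table, repeated in section 6.1.2, has these on-treatment columns: "C1D7 | C1D21 | C3D21 | C5D21", the last marked with a plus sign. Note 4 explains the plus: "Subjects are visited every 6 weeks from V5". Footnotes 9 (blood count), 10 (urinalysis) and 12 (biochemistry) give the same timing: "at C1D7, C1D21, and thereafter at days 21 of every two cycles (odd numbered cycles".

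Extra tests are conditional. Footnote 9 adds blood counts once a low neutrophil or platelet count has been found, and "weekly hemanalysis is required if there is a delay in dosing or dose adjustment due to hematological toxicity". Footnote 12 says patients with early signs of liver injury "before blood biochemical abnormalities should undergo blood biochemistry immediately", and it increases the testing frequency once liver values are raised.

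**The concern.** The dosing rule needs laboratory results every 21 days, and the schedule supplies them every 42 days. Hand-foot reaction, blood pressure and symptomatic toxicity can be judged at the infusion visit. Blood counts, urine protein and symptomless rises in ALT, AST or bilirubin cannot.

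The protocol also directs sites to the flow chart. The part of section 4.5 on subsequent data collection says: "All study procedures are required to be performed according to the time window in the schematic flow diagram". Section 6.1.2 likewise ties examinations to the cycles shown there. A site doing only what the flow chart lists would start cycles 3, 5, 7 and so on with values about one cycle old.

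Several symptomless changes that call for a delay could then go unseen through one more infusion and 14 more days of anlotinib:

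- neutrophils, platelets or hemoglobin below the section 5.5.3.2 limits;
- ALT, AST or bilirubin at grade 2 or higher (section 5.5.3.2 and Table 5.5-4);
- urine protein above 2+ (section 5.5.3.2), or at 2+ with at least 1.0 g per 24 hours (Table 5.5-5).

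A smaller inconsistency touches the same decision. Footnote 10 and the laboratory table in section 8.2.5 call for a 24-hour urine protein measurement after one result of 2+ or more. Section 6.5.6.2 (3) waits for two consecutive ++ results. Under Table 5.5-5 the 24-hour value decides whether a patient at 2+ is delayed.

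**Working it through.** The check is calendar arithmetic, and the protocol states no figure of its own to reproduce.

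**Inputs.** Cycle length is 21 days (section 5.5.1). Scheduled samples fall on C1D7, C1D21 and day 21 of odd-numbered cycles, with a ±3-day visit window (Study Procedures). One month is 30.5 days (section 3.2). Cycles are assumed to run without delay.

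**Age of the latest scheduled result.** Cycle k starts on day 21(k − 1) + 1. Scheduled samples after C1D7 fall on days 21, 63, 105 and so on, a spacing of 63 − 21 = 105 − 63 = 42 days.

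| Cycle start | Day | Latest scheduled sample | Sample day | Age (days) |
|---|---|---|---|---|
| C2D1 | 22 | C1D21 | 21 | 1 |
| C3D1 | 43 | C1D21 | 21 | 22 |
| C4D1 | 64 | C3D21 | 63 | 1 |
| C5D1 | 85 | C3D21 | 63 | 22 |
| C6D1 | 106 | C5D21 | 105 | 1 |
| C7D1 | 127 | C5D21 | 105 | 22 |

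Moving the sample by ±3 days gives 22 − 3 = 19 to 22 + 3 = 25 days at the odd-numbered starts. At nominal timing, that sample predates all of the preceding cycle's dosing.

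**Share of cycle starts affected.** Cycle 1 is covered by screening and even-numbered cycles by the preceding day 21. Among n starts, the uncovered ones are the odd cycles from 3 upward.

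- 9 months (the hypothesised median PFS, taken as time on treatment): 9 × 30.5 = 274.5 days. C14D1 is day 274, so n = 14. Uncovered: C3, C5, C7, C9, C11, C13. 6/14 = 42.9%.
- 5 months (the historical-control median): 152.5 days. C8D1 is day 148 and C9D1 is day 169, so n = 8. Uncovered: C3, C5, C7. 3/8 = 37.5%.
- 12 months: 366 days. C18D1 is day 358 and C19D1 is day 379, so n = 18. Uncovered: odd cycles C3 to C17. 8/18 = 44.4%.

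**Could other text fill the gap?** The note under the schedule says: "The window period of 3 days for screening indicators and examination must be completed before the initiation of the treatment cycle". It governs when scheduled examinations are completed and adds no test at the end of even-numbered cycles. The plus sign on the C5D21 column cannot mean every cycle, because note 4 and the odd-cycle wording in the footnotes exclude that reading. The conditional tests need an abnormal value, liver symptoms, or a hematological delay or dose adjustment first, so they do not detect a new symptomless change.

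**The case against.** The strongest reply is that section 5.5.3.2 is itself binding, so it implies a current test. The schedule forbids no extra samples, and patients attend on day 1 of each cycle for the infusion. Many sites would probably draw blood then. In context, sections 4.5 and 6.1.2 mainly say that interrupted treatment does not shift the timetable; neither calls the flow chart a ceiling. Sections 6.5.1 and 6.5.6.2 (3) also speak of close monitoring. It follows that a careful site can comply with both texts. What remains is that the protocol never tells it to take the sample, and the schedule it points to omits the test. The general statements on monitoring set no visit.

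A second reply is that section 5.5.3.2 does not name ALT, AST or bilirubin, and that its limit on other toxicities may refer to those already known. That has some weight, so blood count and urine protein are the firmest part. But Table 5.5-4 delays anlotinib at grade 2 liver abnormality, and Table 5.5-10 discontinues treatment for hepatitis of grade 3 or worse, defined by laboratory values. Neither rule can be applied to a symptomless patient without a current test.

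Third, the percentages count dosing decisions, and no harm rate is shown. That is correct. The urine-protein inconsistency is also minor, since measuring 24-hour protein after the first 2+ result satisfies both texts.

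**Conclusion.** The concern holds. A stated dosing rule for every cycle conflicts with a stated schedule that serves only every second cycle from cycle 2 onward. From cycle 3, each odd-numbered start relies on a scheduled result 22 days old (19 to 25 with the window). Under uninterrupted treatment this affects 43% of cycle starts over 9 months, with a range of 37.5% at 5 months to 44% at 12 months. These shares rest on the assumed time on treatment and on no dose delays. The document gives no rate of symptomless breaches, so the number of missed delays cannot be estimated.

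This is a patient-safety and operational matter. Dose escalation is unaffected, because the dose-limiting toxicity window is cycle 1, which has samples at C1D7 and C1D21. Sample size, alpha and power do not change.

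**What to change.** Amend footnotes 9, 10 and 12 and both copies of the schedule table (Study Procedures and section 6.1.2) so that blood count, urinalysis and biochemistry are obtained, and the results reviewed, before the day-1 infusion of every cycle. Taken within 3 days before day 1, the result would be 1 to 3 days old instead of about 22.

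In the same amendment, align section 6.5.6.2 (3) with footnote 10 and section 8.2.5, so that a single result of 2+ or more triggers the 24-hour urine protein measurement.

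The cost is a protocol amendment and one extra routine blood and urine sample at just under half of the infusion visits, about six over 9 months. Patients already attend these visits.

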**Table 5.5-2 Dose adjustments related to anlotinib hydrochloride capsules-** **the Platelet counts decreased**

| Grade of AEs | Recommended actions | Adjustment of administration regimens |
| --- | --- | --- |
| Grade 1 | Planned visits | Maintain the original dose |
| Grade 2 | Delayed dosing until recovery to ≤grade 1 | Maintain the original dose |
| Grade 3 | Delayed dosing and medical intervention treatment until recovery to ≤grade 1 | reduce 1 dose level |
| Grade 4 | Permanent termination of treatment | / |

1. Neutropenia

**Table 5.5-3 Dose adjustments related to anlotinib hydrochloride capsules-** **the neutrophil count decreased**

| Grade of AEs | Recommended actions | Adjustment of administration regimens |
| --- | --- | --- |
| Grade 1 | Planned visits | Maintain the original dose |
| Grade 2 | Delayed dosing until recovery to ≤grade 1 | Maintain the original dose |
| Grade 3-4 | Delayed dosing and medical intervention treatment until recovery to ≤grade 1 | reduce 1 dose level |

- Nonhematologic toxicity

1. Abnormal liver function (elevated ALT, AST, or TBIL)

**Table 5.5-4 Dose adjustments related to anlotinib hydrochloride capsules- abnormal liver function**

| Grade of AEs | Recommended actions | Adjustment of administration regimens |
| --- | --- | --- |
| Grade 1 | Planned visits | Maintain the original dose |
| Grade 2 | Delayed dosing until recovery to ≤grade 1 | Maintain the original dose |
| Grade 3-4 | Delayed dosing and medical intervention treatment until recovery to ≤grade 1 | reduce 1 dose level |

1. Proteinuria

**Table 5.5-5 Dose adjustments related to anlotinib hydrochloride capsules- proteinuria**

| Grade of AEs | Definition | Recommended actions | Adjustment of administration regimens |
| --- | --- | --- | --- |
| Grade 1 | Proteinuria 1+, or urinary protein < 1.0g/24 hours | Planned visits | Maintain the original dose |
| Grade 2 | Proteinuria 2+, and urinary protein < 1.0g/24 hours | Planned visits | Maintain the original dose |
|  | Proteinuria 2+, and urinary protein 1.0-3.4g/24 hours | Delayed dosing and medical intervention treatment until proteinuria ≤ 2+ and urinary protein < 1.0g/24 hours | Maintain the original dose |
| Grade 3 | Urinary protein≥3.5g/24hours | Delayed dosing and medical intervention treatment until proteinuria ≤ 2+ and urinary protein < 1.0g/24 hours | reduce 1 dose level |

1. Bleeding events (including hemoptysis, gastrointestinal bleeding, epistaxis, bronchial bleeding, gingival bleeding, gross hematuria, fecal occult blood, and cerebral hemorrhage).

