**Table 5.5-6 Dose adjustments related to anlotinib hydrochloride capsules-bleeding events**

| Grade of AEs | Recommended actions | Adjustment of administration regimens |
| --- | --- | --- |
| Grade 1 | Planned visits | Maintain the original dose |
| Grade 2 | Delayed dosing until recovery to ≤ grade 1 | reduce 1 dose level, if it recurs, permanent termination of treatment is considered |
| ≥Grade 3 | Permanent termination of treatment | / |

1. Hypertension

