Subjects who have received treatment with first or second-generation EGFR TKIs are required to provide a genetic testing report, proving the absence of primary or acquired *T790M* mutations. Subjects who have received treatment with third-generation EGFR TKIs are required to provide a genetic testing report, proving the positivity of EGFR mutations. For subjects with access to tissue samples, it is recommended to prioritize tissue-based *EGFR* mutation testing. Subjects without access to tissue samples may choose blood-based *EGFR* mutation testing using traditional gene testing (such as ddPCR, Arms-PCR, etc.) or high-throughput sequencing. T790M mutation and Exon 20 insertion mutation are key sites for testing.

PD-L1 expression is measured in suitable subjects from sub-centers with testing conditions.The selected subjects should meet the criteria for biopsy, and it is anticipated that sufficient tissue will be obtained for immunohistochemistry. Fresh tissue is divided into two parts, with one directly used for the immunohistochemistry of PD-L1, and the other prepared into a paraffin block for TMB testing.

- 1. Maximum tolerated dose and dose-limiting toxicity

MTD: Toxicity and safety are observed to determine the MTD of anlotinib when combined with TQB2450. MTD is defined as the highest dose when less than 33% of subjects experienced DLT.

DLT: DLT is defined as any one of the following toxicities occurring within the first 21 days of treatment (including events that started in the first cycle but were confirmed in the second cycle), as per NCI CTCAE 5.0.

1. Grade IV hematologic toxicity and following events:
2. ≥ CTCAE grade 3 febrile neutropenia (ANC<1000/ul; body temperature ≥38.5°C)
3. ≥ CTCAE grade 3 neutropenia lasting for >7 days
4. CTCAE grade 3 platelet count decreased lasting for >7 days, with signs of clinically significant bleeding or need for platelet transfusion
5. Grade II or higher liver and kidney dysfunction (lasting for >7 days after symptomatic treatment) and following events:
6. CTCAE grade 2 bilirubin increased, lasting for >7 days
7. ≥ CTCAE grade 3 bilirubin increased
8. CTCAE grade 3 AST or ALT increased, lasting for >7 days
9. CTCAE grade 4 AST or ALT increased
10. Grade III or higher non-hematologic toxicity (except for alopecias) and following events:
11. ≥CTCAE grade 2 pancreatitis
12. Cerebral hemorrhage, ≥grade 2 pulmonary hemorrhage
13. grade 2 abnormal coagulation or bleeding, lasting for >7 days

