14. CTCAE grade 3 fatigue, lasting for >7 days
15. CTCAE grade 3 hypertension, hand-foot skin reaction, diarrhea, nausea, and vomiting that are not relieved by symptomatic treatment until the next treatment cycle.
16. CTCAE grade 3 abnormal laboratory examinations that are not relieved by symptomatic treatment until the next treatment cycle.

If one subject experiences toxicity that met the criteria for DLT, the study treatment was interrupted and follow-up was performed as described in the study procedures. Treatment can be discontinued due to any DLT. However, under the investigator and co-sponsor approval, subjects with DLT could receive the next lowest dose level after recovery.

- 1. Efficacy assessment
     1. Primary endpoint
- **Progression-free survival:**

PFS is defined as the time from enrollment to the first time of PD or death from any cause, whichever occurs first.

If the subject did not experience disease progression or death, PFS is defined as the date of the last confirmed progression-free. Subjects who discontinued for reasons other than disease progression (no subsequent tumor imaging assessment) and starting subsequent therapy after the trial were censored at the time of discontinuation or the initiation of subsequent therapy. In cases other than those described above, pre-planned sensitivity analyses will undertake to define PFS based on the date of confirming imaging progression events. New onset other tumor is not considered indicative of PD and is not censored as data.

If the image examination and assessment show PD, the date of PD is not defined as the imaging time of first signs of PD, but the time of definite imaging evidence of PD. If the PD is diagnosed with other clinical examinations, the date of PD is defined as the diagnosis time.

- - 1. Secondary endpoints
- **OS:** OS is defined as the time from enrollment to the date of death due to any cause. For the analysis of OS, data for patients who are alive will be censored for OS at the time of the last follow-up. Data for patients who were lost to follow-up will be censored for OS at the last date they were known to be alive. Censored OS is defined as the time from randomization to censor.
- **1-year PFS rate:** 1-year PFS rate is defined as the percentage of patients who have not progressed or died at 1 year.
- **1-year OS rate:** 1-year OS rate is defined as the percentage of patients who are still alive at 1 year.

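### A grade 1 cerebral hemorrhage in phase I cycle 1 keeps full-dose anlotinib under Table 5.5-6 but is most naturally a DLT under section 6.3, and the protocol does not say which applies

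*Protocol*

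**What the plan says.** **Dose tables (section 5.5, Dose modification).** Table 5.5-6 is introduced as covering "Bleeding events (including hemoptysis, gastrointestinal bleeding, epistaxis, bronchial bleeding, gingival bleeding, gross hematuria, fecal occult blood, and cerebral hemorrhage". Its grade 1 row reads "Grade 1 | Planned visits | Maintain the original dose", with no exception by bleeding site. Grade 2 delays dosing and reduces anlotinib by one level. The last row reads "≥Grade 3 | Permanent termination of treatment". The general principles of the same section make these rules optional for the investigator, who may depart from them after consulting the sponsor. They are not limited to a phase or a cycle.

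**DLT rules (section 6.3).** Among the events added to the grade III or higher non-hematologic criterion is "Cerebral hemorrhage, ≥grade 2 pulmonary hemorrhage". Items beside it carry a grade: "≥CTCAE grade 2 pancreatitis" and "grade 2 abnormal coagulation or bleeding, lasting for >7 days". The consequence for the patient is: "If one subject experiences toxicity that met the criteria for DLT, the study treatment was interrupted and follow-up was performed". Discontinuation is allowed for any DLT. Re-treatment is an option: "under the investigator and co-sponsor approval, subjects with DLT could receive the next lowest dose level after recovery".

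**Synopsis (Study Design).** The short DLT definition requires a drug-related event. For non-hematologic toxicity other than hepatic or renal dysfunction it requires grade 3 or higher. Cerebral hemorrhage is not mentioned.

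**The concern.** One list treats a brain bleed like a nosebleed or bleeding gums, and at grade 1 recommends no change. Another list singles it out as dose-limiting. A site that opens the bleeding table first would continue full-dose anlotinib, an anti-angiogenic drug, after an intracranial bleed. A site that opens section 6.3 first would interrupt treatment and need approval to resume at a lower level. The safety of that patient is the main stake.

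There is also a smaller effect on counting. Under section 6.1, one DLT among three patients triggers three more at the same dose, whereas none allows escalation (or, at 12 mg, fixes that dose for stage 2). A grade 1 event counted under section 6.3 but not under the synopsis could therefore change that step.

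**Working it through.** The protocol gives no figure on this point, so the check is a comparison of texts.

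**Step 1. Does the table reach the event?** Yes. Cerebral hemorrhage is named in the introduction to Table 5.5-6, and the grade 1 row makes no exception. The cycle-start conditions in section 5.5 (Criteria for Dose Delay) do not catch it either, because toxicities not listed separately need only have recovered to grade 1 or lower.

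**Step 2. Does section 6.3 reach a grade 1 event?** Most naturally yes.
- The grade 2 threshold in that line stands after cerebral hemorrhage and is attached to pulmonary hemorrhage.
- The parent criterion already makes every grade III or higher non-hematologic toxicity a DLT, so naming cerebral hemorrhage would add nothing if it counted only from grade 3.
- This remains an inference. Some later items under the same heading, such as grade 3 fatigue lasting more than 7 days, narrow the parent criterion rather than add to it.

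**Step 3. Compare by grade, phase I, first 21 days.**
- *Grade 1.* Table: scheduled visits, original dose. Section 6.3: interruption, then at most the next lowest level, after recovery and with approval. These differ.
- *Grade 2.* Both delay or interrupt, and both lead to one level lower for anlotinib. The match is limited to the anlotinib level. Section 6.3 interrupts study treatment, which includes TQB2450, and requires approval to resume. The table concerns anlotinib only and has no approval step.
- *Grade 3 or higher.* The table terminates permanently. Section 6.3 permits discontinuation for any DLT and makes re-treatment optional. Terminating satisfies both, so there is no conflict.

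**Step 4. Is precedence stated?** No sentence in sections 5.5, 6.1 or 6.3 ranks one text above the other.

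**Step 5. Can such an event come to light in the window?** Yes. The imaging note in section 6.1 provides for patients with stable brain metastases, and the visit schedule places brain MRI at cycle 1 day 21. Section 6.3 also counts events that began in cycle 1 and were confirmed in cycle 2. Anlotinib is given for two weeks and stopped for one, so a finding at day 21 bears on the cycle 2 dose.

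**The case against.** The strongest reply is that ordinary reading settles the matter. The tables are optional, section 6.3 is specific to DLTs, and a site that interrupts under section 6.3 breaches nothing. The day 21 scan falls at the end of the DLT observation period, when the team must assess the patient against section 6.3 anyway, and in the scheduled week off anlotinib. This lowers the practical risk. It does not remove the defect: the written default in the table is still to continue at full dose, departing from it is the step that calls for sponsor consultation, and the protocol nowhere says that section 6.3 governs.

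A second reply is that the tables may not be meant for phase I. Section 5.5 ties the dose ladder to the MTD, which does not yet exist during escalation, and section 6.1 says only that examinations and follow-up are shared with stage 2. That suggests such a limit but does not state it.

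Third, the any-grade reading is an inference, and under the synopsis definition a grade 1 bleed is not a DLT at all. Both statements are right. The second shows that the protocol holds two DLT definitions, which is itself a reason to align them.

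Fourth, the group at risk is small and perhaps empty. Brain metastases that are symptomatic or only recently controlled, and a cerebral vascular accident within 6 months, are excluded. The synopsis also describes 12 mg as already determined in phase I. If escalation is complete, no patient remains in the window, although sections 3.1 and 5.5 still leave the dose to be set by phase I.

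**Conclusion.** The point holds in a narrow form: a low-severity safety inconsistency for a grade 1 cerebral hemorrhage in the first 21 days of phase I. It concerns at most 3 to 18 patients. The documents give no rate for the event and none is assumed. The phase II sample size of 54 and the PFS analysis are unaffected. The conclusion rests on two assumptions: that an item listed without a grade means any grade, and that the dose tables are open to use during escalation.

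Three stronger readings are tempting and not supported:
- *That the texts also contradict each other at grade 3 or higher.* They do not, since section 6.3 allows discontinuation for any DLT and re-treatment is only an option.
- *That the lost anlotinib exposure can be calculated per dose level, with a patient at 8 mg losing all of it.* That would apply a ladder defined from the MTD to patients treated before an MTD exists, and section 5.5 does not clearly extend it to them.
- *That every grade 1 cerebral bleed in any cycle must interrupt anlotinib.* Outside phase I cycle 1 the passages do not conflict, so this is a clinical choice for the sponsor.

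**What to change.** Three edits, in one amendment:

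1. In the grade 1 row of Table 5.5-6, except cerebral hemorrhage when the event meets a DLT criterion in phase I cycle 1.
2. Add a sentence saying that for such events the handling in section 6.3 applies (interruption, then resumption no higher than the next lowest level, after recovery and with investigator and co-sponsor approval), and that the table's permanent termination at grade 3 or higher still stands.
3. Have the synopsis DLT definition refer to section 6.3, so that one definition governs both patient management and cohort decisions.

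No visits, tests or patients are added. The downside is that an occasional patient with an asymptomatic bleed loses some anlotinib exposure. If escalation is already complete, the first two edits affect no remaining patient, and the sponsor may simply decide whether the grade 1 row is acceptable for cerebral bleeding in later cycles and in phase II.
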